### Measurements

Assessments will consist of demographic information and three major parts: (1) fidelity checking measures, including mindsets of negative emotions and intervention feedback, which involves Likert-scale rating of the acceptability of the intervention and open-ended questions for feedback; (2) primary outcome measures, including perceived control over anxiety, attitude toward help-seeking, and hopelessness; (3) secondary outcome measures, including the psychological wellbeing, physical activity, depression, anxiety, and stress symptoms. Two attention-checking items are embedded in all assessment points’ surveys to screen careless responding.

### Content fidelity checking

*Mindsets of negative emotions* will be assessed by the well-validated Mindset of Depression, Anxiety, and Stress Scale (MDASS) in Chinese [22]. It involves three subscales (i.e., mindsets regarding depression, anxiety, and stress), and each subscale includes 4 items. There are items such as “*When you have a certain level of depression/anxiety/stress, you really cannot do much to change it*.” Participants will rate the 12 items on a 6-point Likert scale (1 = *strongly disagree* to 6 = *strongly agree*). Higher scores represent that participants less believe in the malleability of negative emotions. Good reliabilities of three subscales were reported with Cronbach’s alphas equaling 0.91, 0.89, and 0.90, respectively [22].

*Intervention feedback* will be measured by the self-developed intervention feedback scale referring to the theoretical framework of acceptability (TFA). Seven aspects are involved for consideration, i.e., affective attitude, intervention coherence, burden, opportunity costs, perceived effectiveness, self-efficacy, and ethicality [29]. Six items are developed for each component except ethicality. Besides, the current scale integrates four items and an open-ended written question from the Program Feedback Scale [30] to measure the intervention’s acceptability. Participants will rate these 10 items on a 5-point scale. One example item is “*How acceptable was the intervention to you?*”.

*Motivation* will be measured by self-developed items. Two items are utilized to measure motivation at changing current emotional status before the intervention, including “*How much do you want to change your current emotional state*” and “*How much do you want to improve your emotion regulation ability*”. It is a 6-point Likert scale from 1 (*not at all*) to 6 (*to a very large extent*). Three items are right after the intervention program, measuring the motivation to apply contents learned from the intervention, including “*After the intervention, I have more confidence in emotion regulation abilities*,” “*After the intervention, I want to apply the emotion regulation strategies*,” and “*After the intervention, I want to improve my emotion regulation abilities*.” Participants will need to rate on a 6-point Likert scale from 1 = *strongly disagree* to 6 = *strongly agree*. Higher scores represent that participants have higher motivation to change current emotional status before the intervention and apply what they have absorbed after the intervention.

### Primary outcome

*Perceived control over anxiety* will be assessed by the Emotion Control subscale of the 15-item Anxiety Control Questionnaire (ACQ-EC) [31]. The subscale has five items (e.g., I can usually put worrisome thoughts out of my mind easily), including one reversed item (i.e., *When I am anxious, I find it hard to focus on anything other than my anxiety*). Participants will rate the items on the scale from 0 = *strongly disagree* to 5 = *strongly agree*. Higher scores on anxiety control were found to be associated with lower levels of anxiety [32]. The Cronbach’s alpha was 0.73 [31].

### Secondary outcomes

*Attitude toward help-seeking* will be measured by five items, including two items from the Attitude toward Seeking Professional Psychological Help Scale (ATSPPH) [33] and three self-developed items. The ATSPPH has good reliability with Cronbach’s alpha equaling 0.72 [33], with a sample item from ATSPPH of “*If I believed I was having a mental breakdown, my first inclination would be to get professional attention*.” Three self-developed items include “*When I encounter difficulties, I will not ask help from teachers*,” “*When I encounter difficulties, I will not ask help from social workers/counselors*,” and “*Professional counseling and treatments can help people improve mental health*.” Participants will need to rate the degree of help-seeking on a 6-point Likert scale, ranging from 1 = very untrue of me to 6 = very true of me.

*Psychological well-being* will be measured by the short version of the 14-item Warwick-Edinburgh Mental Well-being Scale (WEMWBS-14) [34, 35]. Participants will need to rate on a 5-point Likert scale to report general well-being states, ranging from 1 (*none of the time*) to 5 (*all of the time*) on items such as “*I have been feeling optimistic about the future*.” A higher average score of all items represents a higher level of psychological well-being among the participants. Good reliability was reported with Cronbach’s alpha of 0.89 [35].

*Physical activity* will be measured by the Chinese version Global Physical Activity Questionnaire (GPAQ) [36], which involves 16 questions of three domains (i.e., activity at work, for transportation, and for recreation). Three questions in the recreational activity domain are used in this study such as “*Do you do any vigorous-intensity sports, fitness, or recreational (leisure) activities that cause large increases in breathing or heart rate like running or football, for at least 10 min continuously?*”. Participants will be asked to report the frequency and duration of physical activities in a typical week.

*Anxiety symptoms* will be assessed by the Chinese version of the Generalized Anxiety Disorder-7 (GAD-7) scale [37, 38] to measure in the past 2 weeks the frequency of being bothered by anxiety symptoms. Participants will be asked to report the frequency from 0 (*not at all*) to 3 (*nearly every day*) on items such as “*Not being able to stop or control worrying*.” The overall scores of all the 7 items indicate the severity of anxiety symptoms: ranging from 0 to 5 means no anxiety symptom, ranging from 5 to 9 means mild anxiety, ranging from 10 to 14 means moderate anxiety, and ranging from 15 to 21 means severe anxiety. Good reliability was reported with Cronbach’s alpha equaling 0.93 [23].

*Depressive symptoms* will be measured by the Chinese version of the Patient Health Questionnaire-9 (PHQ-9) [39, 40] to assess the frequency in the past two weeks of participants being bothered by depressive symptoms. For example, there is an item “*Feeling down, depressed or hopeless*.” Participants will need to report the frequency from 0 (*not at all*) to 3 (*nearly every day*) on items such as “*Feeling down, depressed or hopeless*.” The overall scores of all the 9 items indicate the depression level: ranging from 0 to 5 means no depressive symptom; ranging from 5 to 9 means mild depression; ranging from 10 to 14 means moderate depression, ranging from 15 to 19 means moderately severe depression, and ranging from 20 to 27 means severe depression. The Cronbach’s alpha was 0.85 [23].

*Stress symptoms* will be measured by the Chinese version of the 4-item Perceived Stress Scale (PSS-4) [41, 42] including items such as “*In the last month, how often have you felt that you were unable to control the important things in your life?*”. Participants will need to report the perceived stress level in the previous month, ranging from 0 (*never*) to 4 (*very often*), including two reversed items ranging from 0 (*very often*) to 4 (*never*). A higher summed score means a higher level of self-perceived stress. The Cronbach’s alpha was 0.83 [43].

*Hopelessness* was measured by the helplessness subscale of the Chinese version Demoralization Scale [44, 45]. Participants will be asked to rate the 4 items such as “*I feel hopeless*” on a 5-point Likert scale from 0 = *strongly disagree* to 4 = *strongly agree*. A higher mean score indicates a higher level of hopelessness. A Cronbach’s alpha of 0.72 was reported in the previous study [44].

*Socio-demographic information* includes an array of participant characteristics and is measured at baseline to examine the variability between groups: gender, age, university name, major, grade, ethnicity, education level of parents, whether having siblings, and perceived socio-economic status.

### Data analyses

An intention-to-treat analysis will be conducted, and multiple imputation will be applied to handle the missing data. Descriptive statistics will be used to demonstrate the socio-demographic and all baseline outcome variables by study arms. Outcome variables will be compared between the arms using *t*-tests, one-way analysis of variance. Generalized estimating equations (GEE) will be used for follow-up data over time. Subgroup analysis will be conducted to test the differences among participants of different gender, motivation, and feedback about the intervention and among participants with different levels of anxiety and depression. Two-level analyses are to be conducted since cluster randomization is used [46]. The group effect, the time effect, and the time-by-group interaction effect on the primary and secondary outcomes will be tested with multilevel regression. A *p*-value of < 0.05 signifies statistical significance, and all statistical analyses will be conducted with SPSS Version 26.

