**Methods:**

University students (*N* = 250, ages 18–25) from universities in the Greater Bay Area will be randomized to either the brief digital growth mindset intervention group or the waitlist control group. Participants will report on the mindsets of negative emotions, perceived control over anxiety, attitude toward help-seeking, physical activity, hopelessness, psychological well-being, depression, anxiety, and perceived stress at baseline and the 2-week and 8-week follow-ups through web-based surveys. A 30-min digital intervention will be implemented in the intervention group, with a pre- and post-intervention survey collecting intervention feedback, while the control group will receive the link for intervention after 8 weeks.

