### Hypotheses

We hypothesize that the brief digital growth mindset intervention is effective in the primary outcome of (i) enhancing perceived control over anxiety and secondary outcomes of (ii) increasing attitude toward help-seeking, (iii) reducing hopelessness, (iv) enhancing psychological well-being, (v) increasing physical activities, and (vi) reducing depressive, anxiety, and stress symptoms. Moreover, the effectiveness is hypothesized to be greater among participants with higher anxiety and depression symptom, or higher motivation at changing current emotional status and emotion coping than among those with low or no symptoms or motivation.

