### Brief digital growth mindset intervention and waitlist control group

The randomized controlled trial is designed to demonstrate the superiority of the intervention group to the waitlist group with a 1:1 allocation. The intervention is a web-based intervention, which is adapted from the single-session growth mindset intervention (SIGMA) for secondary school students developed by Zhu et al. [26]. The current intervention adapted the SIGMA intervention content for university students (U-SIGMA) and incorporated boosters to strengthen the effectiveness of the intervention. The U-SIGMA contains five components: (a) introduction of emotional brain to communicate scientific knowledge on emotion and growth mindset regarding emotion, (b) stories and testimonials from university students describing how growth mindsets or fixed mindsets affect their coping with mental health symptoms, (c) emotion coping strategies, (d) common misconceptions and doubts of growth mindset, and (e) self-persuasion writing exercises for participants to share notes on the negative emotion growth mindset with others. Boosters with key messages of intervention are made through e-posters, which will be sent to all participants in the intervention group as reminders weekly from the second week after the intervention through email, WhatsApp, or WeChat, with a total of four times. Besides, boosters will be designed based on the “saying is believing” mechanism, empowering and encouraging the participants to share what they learned with others for knowledge reflection and application. For example, several blanks will be left for the participants to critically think about and write down their own emotional coping strategies or others’ examples of growth mindset based on daily observation. Participants in the waitlist control group will not receive the intervention program until 8 weeks later, though they will be asked to complete three repeated measures at the same time as the intervention group. Figure 2 presents the Standard Protocol Items: Recommendations for Interventional Trial (SPIRIT checklist) about the schedule of enrolment, interventions, and assessments.

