## Discussion

This study is to evaluate a randomized trial of a brief digital growth mindset intervention on enhancing Chinese university students’ help-seeking and sense of control over mental health in the Greater Bay Area. Previous research provided strong empirical evidence about the association between growth mindsets regarding negative emotions and mental health [23–25], yet no intervention study provide supports on its effectiveness on promoting mental health among university students. Besides, the single-session brief digital intervention was demonstrated to be effective, which is comparable to interventions that take several months, and the effects exist even after a 9-month follow-up [28]. Therefore, we anticipate that the brief digital growth mindset intervention, which instills the belief-in-change regarding negative emotions, will significantly enhance participants’ perceived control over anxiety and help-seeking tendency, increase psychological well-being, proactive coping, such as physical activity, and reduce hopelessness, depression, anxiety, and stress symptoms. Moreover, the subgroup analysis will help identify the effectiveness and acceptability in specific groups of participants.

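### Feedback about the intervention exists only in the intervention arm and only after randomization, so it cannot define a subgroup for the treatment effect; the plan should also say which motivation items define the motivation subgroup

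*Protocol article*

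**What the plan says.** The Data analyses section of the protocol article plans: "Subgroup analysis will be conducted to test the differences among participants of different gender, motivation, and feedback about the intervention", together with subgroups by level of anxiety and depression. All these factors are listed as if they were of one kind. The Discussion gives the purpose: "the subgroup analysis will help identify the effectiveness and acceptability in specific groups of participants".

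On who provides feedback and when, the abstract's Methods paragraph says: "A 30-min digital intervention will be implemented in the intervention group, with a pre- and post-intervention survey collecting intervention feedback". The section on the intervention and the waitlist adds: "Participants in the waitlist control group will not receive the intervention program until 8 weeks later". The feedback items, described under Content fidelity checking, ask for a rating of the programme itself.

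Motivation is measured twice, also under Content fidelity checking. First: "Two items are utilized to measure motivation at changing current emotional status before the intervention". Then: "Three items are right after the intervention program, measuring the motivation to apply contents learned from the intervention". The Data analyses section does not say which set forms the subgroup. The Hypotheses section expects a larger effect in participants with "higher motivation at changing current emotional status and emotion coping than among those with low or no symptoms or motivation".

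**The concern.** A subgroup analysis of a treatment effect compares the arms within levels of a factor. The comparison stays randomized only if the factor is fixed before allocation and known in both arms. Gender and baseline symptom level meet this condition. Feedback does not: it is given after allocation, may itself depend on how the participant responds, and has no control counterpart before the last outcome at 8 weeks.

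Students who rate the programme highly may well be those who were already doing better or were improving anyway. If their outcomes are set against all controls, or against those of low raters, the result can look like greater effectiveness in students who liked the programme even when the programme does nothing. That conclusion would be easy to publish and easy to act on. The three motivation items asked after the programme have the same defect.

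**Working it through.** **The plan's own figure.** For d = 0.40, 80% power and two-sided alpha 0.05 (Sample size section): n per arm = 2(1.960 + 0.842)² / 0.40² = 98.1, so 99. The t-test version gives 99.08, so 100 per arm and 200 in total. With 20% attrition, 200 / (1 − 0.20) = 250. The stated 200 and 250 reproduce, and nothing below changes them.

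**Which factors are available in which arm before week 8**

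| Factor | Intervention arm | Waitlist arm | Fixed before randomization? |
|---|---|---|---|
| Feedback | after the session | cannot exist | no |
| Three post-programme motivation items | after the session | cannot exist | no |
| Two pre-intervention motivation items | yes | not stated in the article | yes, if asked before the Randomizer |

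For the first two rows an arm-by-factor interaction cannot be estimated, because the factor is undefined in one arm.

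**Size of the false effect.** Assumptions, none of them from the article except the 100 per arm: 100 completers per arm, true effect zero, outcome normal with SD 1 and scored so that higher is better, and feedback split at its median. Feedback correlates r with the follow-up outcome, with r varied from 0.1 to 0.5.

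- High-feedback half minus all controls: r × √(2/π) = 0.798 r. At r = 0.3 this is 0.24 SD, and 0.24 / 0.40 = 60% of the planned effect.
- High minus low feedback within the arm: 2 × 0.798 r. At r = 0.3 this is 0.48 SD.

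The rejection rates come from a simulation of 20,000 trials for each r, with a t-test at two-sided 5%:

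| r | False difference, high feedback vs controls (SD) | Significant, high feedback vs controls | Significant, high vs low within arm |
|---|---|---|---|
| 0 | 0.00 | 5% | 5% |
| 0.1 | 0.08 | 7% | 12% |
| 0.2 | 0.16 | 15% | 35% |
| 0.3 | 0.24 | 28% | 68% |
| 0.5 | 0.40 | 65% | 99% |

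At r = 0.5 the false difference equals the planned d of 0.40.

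**Check on a valid factor.** If the factor is measured in both arms before randomization, the mean difference between arms in the high half is 0.00. The rejection rate is 5.4% at r = 0.3 and 6.0% at r = 0.5. The small excess over 5% comes from splitting each arm at its own median. The bias therefore comes from when and in whom the factor is measured, and not from a correlation with the outcome as such.

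**The case against.** **Feedback could be meant descriptively.** The sentence speaks of differences among participants and does not announce a comparison of high raters with controls. Feedback is not a moderator in the Hypotheses section, and acceptability is a separate objective. A description within the intervention arm is a possible reading, and it would be sound. But the article lists feedback beside gender and symptom level and gives effectiveness as a purpose of the subgroups, so the text does not confine feedback to that use.

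**Motivation.** A reader might infer that the whole motivation subgroup lacks a randomized comparison, or that controls never answered the two pre-intervention items. The article does not support either. The hypothesis describes nearly the same construct as those two items, whereas the later three concern applying what was learned. The abstract's list of baseline measures omits motivation, but it also omits the socio-demographic data that the Measurements text places at baseline, so its silence proves little. The assessment schedule is a figure that is not available here. The objection stands on this point: what remains is an unspecified choice of items.

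**Size.** The correlation is an assumption, and the size depends on it. The 68% within the arm is the chance of detecting an association assumed to be real, and it becomes a false effect only if it is reported as effectiveness. The calculation also concerns follow-up level. If high raters were better by the same amount at baseline, the difference would cancel in the planned time-by-group contrast, and only differences in change would bias that contrast. These limits are fair. They narrow the size but do not make the subgroup valid. A correlation of exactly zero is implausible for a scale that covers perceived effectiveness and self-efficacy.

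**Conclusion.** The point holds for feedback: it cannot be an effect subgroup, because no control has a value during the comparison and every available contrast is non-randomized. With zero true effect and an assumed correlation of 0.1 to 0.5, comparing high raters with controls on follow-up level gives a false difference of about 0.08 to 0.40 SD, significant in about 7% to 65% of trials against a nominal 5%.

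For motivation the point is conditional. The subgroup is invalid if built on the three post-programme items, and valid if built on the two earlier items and both arms answered these before randomization. The article leaves this open.

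Severity is moderate. These are secondary analyses, and the primary comparison and the sample size are untouched.

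**What to change.** - Remove feedback and the three post-programme motivation items from the effect subgroups. Report them as descriptive associations within the intervention arm, with a statement that they do not show differential effectiveness.
- Define the motivation subgroup as the two pre-intervention items, and state whether both arms answered them before the Randomizer.
- If they did, test the motivation hypothesis as an arm-by-baseline-motivation interaction. If they did not, declare that hypothesis untestable in this trial.

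The cost is a change of wording. What is lost is a feedback effect analysis that has no valid interpretation. Moving items ahead of the Randomizer is not part of the fix. Recruitment was to end about 31 August 2023 and the article appeared on 8 November 2023, so such a move is unnecessary if both arms were asked and too late if they were not.

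The motivation analysis should be reported as having limited precision. In one half of the sample (50 per arm), power for d = 0.40 is about 52%.

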## Methods

### Study design

For this randomized controlled trial study, invitations for participation will be sent to the teachers of six universities in the Greater Bay Area, and then they will be asked to forward the invitation to WhatsApp or WeChat student groups. We also recruit through mass email and promotion posters. Students who click on the research link will be invited to read the research information sheet and sign the consent form, and the survey will immediately end for those students who do not agree to participate in the study without signing the consent. *Qualtrics* in Cantonese and *WenJuanXing* survey tool in Mandarin will be used for Hong Kong students and Mainland students respectively. Participants will be randomized into the intervention group or the waitlist control group by adding a “Randomizer” block into the survey flow of two online survey platforms. The expected allocation ratio and concealment can be ensured since the “Randomizer” block will only appear after the baseline assessments have been completed by the participants and conduct the allocation based on a predetermined ratio. Participants assigned to the intervention group will start the intervention instantly, and those in the control group will receive the intervention link after 8 weeks. Three repeated assessments of the measures will be conducted for two groups simultaneously at (i) baseline, (ii) 2-week post-intervention, and (iii) 8-week post-intervention via survey systems *Qualtrics* (for Hong Kong students) and *WenJuanXing* (for mainland students). The design of 2-week and 8-week post-tests is based on the extant studies on single-session or brief intervention [12, 27]. Invitations for follow-up surveys will be sent to the participants who complete the survey at baseline. Each participant will receive incentives (e-voucher or online red packet) with approximate values of US $5 and US $8 when completing the 2-week and 8-week follow-up questionnaires respectively. Thus, the total compensation for participation is US $13. Incentives will be sent to the participants automatically through the online system excluding invalid responses after the screening. The study flow is seen in Fig. 1.

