### Sample size

The sample size was calculated based on a small-to-medium effect size of *Cohen’s d* = *0.40* from prior research [28], power of 0.80, and alpha of 0.05 (two-tailed). It shows a total of 200 participants (100 per arm) are needed. Referring to the attrition rate of around 20% in our previous school-based studies, it is safe to include 250 participants for this study (125 per arm).

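### Several analyses of the same outcomes are planned at p < 0.05 with no deciding test or time point, and no stated model adjusts for baseline score or randomizing platform

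*Protocol article*

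**What the plan says.** The Data analyses section of the protocol article describes three kinds of analysis:

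- "Outcome variables will be compared between the arms using" t-tests and one-way analysis of variance. This sentence comes straight after the one on baseline descriptives.
- "Generalized estimating equations (GEE) will be used for follow-up data over time".
- "The group effect, the time effect, and the time-by-group interaction effect on the primary and secondary outcomes will be tested with multilevel regression".

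A single significance threshold, p < 0.05, is given for everything. The section also calls for two-level analyses on the ground of cluster randomization, without saying what the second level is.

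The Study design section sets assessments at baseline, 2 weeks and 8 weeks. Allocation comes from a randomizer placed as a "block into the survey flow of two online survey platforms": Qualtrics for Hong Kong students and WenJuanXing for mainland students. The randomizer appears only once the baseline assessment is complete.

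The Sample size section assumes d = 0.40, 80% power and two-sided alpha 0.05, and concludes: "It shows a total of 200 participants (100 per arm) are needed". This becomes 250 after 20% attrition.

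**The concern.** The primary outcome, the ACQ-EC score, can be tested in several ways under this text, and the text does not say which result counts. The candidates do not estimate the same thing. A single-visit comparison, a follow-up average, an interaction and a group main effect can disagree, and a reader of the results could not tell whether the reported one was chosen in advance.

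Two of the listed effects cannot serve as the treatment effect in a three-visit model. The time effect does not compare the arms. The group effect depends on coding. With baseline as the reference visit it is the difference at baseline, which randomization makes zero in expectation. Averaged over visits, it includes one visit at which no effect can exist. Listing ANOVA beside the t-test adds nothing, because with two arms they are the same test.

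The plan also leaves precision unused. Every randomized participant has a baseline score, yet no model is stated to adjust for it. Allocation is generated separately inside each platform, which makes platform in effect a randomization stratum, but it is not named in any model.

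**Working it through.** **Inputs from the protocol article:** d = 0.40, two-sided alpha 0.05, 80% power, 100 evaluable per arm, 20% attrition (Sample size); visits at baseline, 2 and 8 weeks (Study design).

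**Assumptions, not in the document:** SD of 1 at each visit; the same correlation r between any two visits, ranging from 0.3 to 0.7; the same effect, 0.40, at both follow-ups.

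**Reproducing the plan's figure.** n per arm = 2(1.960 + 0.842)²/0.40² = 98.1, so 99. The t-based calculation gives 100 per arm, 200 in all, and 200/0.80 = 250. The stated size is therefore correct for an unadjusted comparison of two groups at one visit.

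**Power of each candidate.** Power is Φ(δ√(n/2)/σ − 1.960) with n = 100 per arm; the noncentral t gives values lower by at most about 0.005. The quantities are:

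- Unadjusted single visit: δ = 0.40, σ = 1.
- Adjusted single visit: δ = 0.40, σ² = 1 − r².
- Unadjusted follow-up average: δ = 0.40, σ² = (1 + r)/2.
- Adjusted follow-up average: δ = 0.40, σ² = (1 + r)/2 − r².
- Group effect averaged over three visits: δ = 0.40 × 2/3 = 0.267, σ² = (1 + 2r)/3.
- Joint time-by-group interaction: F test on 2 degrees of freedom, using both changes from baseline.

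| Contrast | r = 0.3 | r = 0.5 | r = 0.6 | r = 0.7 |
|---|---|---|---|---|
| Single visit, unadjusted | 0.807 | 0.807 | 0.807 | 0.807 |
| Single visit, baseline-adjusted | 0.843 | 0.904 | 0.942 | 0.977 |
| Follow-up average, unadjusted | 0.939 | 0.904 | 0.885 | 0.866 |
| Follow-up average, baseline-adjusted | 0.966 | 0.979 | 0.989 | 0.997 |
| Joint interaction | 0.688 | 0.835 | 0.911 | 0.971 |
| Group effect over three visits | 0.733 | 0.637 | 0.596 | 0.559 |

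**Comparing across contrasts.** An adjusted single visit beats an unadjusted follow-up average only if 1 − r² < (1 + r)/2, that is (2r − 1)(r + 1) > 0, so r > 0.5. At r = 0.5 they tie.

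**Platform.** At r = 0.5, if platform explains a further 2%, 5% or 10% of variance (assumed), power of the adjusted single-visit test moves from 0.904 to 0.912, 0.922 or 0.939. If the sites do not differ, it adds nothing.

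**False positives if any listed test may be claimed.** Simulation with no treatment effect, 100 per arm, r from 0.3 to 0.7:

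| Tests counted | Chance of at least one p < 0.05 |
|---|---|
| 8-week t-test, follow-up average, joint interaction | about 0.11 |
| t-tests at 2 and 8 weeks, follow-up average, group effect, joint interaction | 0.13–0.15 |
| As above, with an interaction contrast at each visit in place of the joint one | 0.17–0.19 |
| No t-tests: follow-up average, group effect, joint interaction | about 0.11 |

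**The case against.** Several parts of the case against this point stand.

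- **The t-tests may be baseline comparisons.** Their sentence follows the baseline descriptives, so this reading is open. It does not remove the problem: GEE and the multilevel effects remain without a ranking, and the last line of the simulation still gives about 0.11.
- **A planned analysis may already be stronger than an adjusted single visit.** A reader might infer that a baseline-adjusted 8-week test would raise power over anything now planned. The figures do not support that. An unadjusted GEE average of the two follow-ups has more power when r is below 0.5. Adjustment helps for the same contrast; it does not make every adjusted contrast better than every unadjusted one.
- **The interaction already uses baseline.** This is true if the multilevel model covers all three visits. From r = 0.6 upward, the joint interaction comes within about three points of the adjusted single-visit test (0.911 against 0.942; 0.971 against 0.977). At r = 0.3 it is well below (0.688 against 0.843).
- **Platform may already be absorbed.** If the second level of the two-level analyses is university, platform is essentially contained in it. The text does not say, so one cannot assert that every analysis omits it.
- **Listing group, time and interaction is ordinary model description.** Nothing in the text makes the group effect decisive. The low power is a reason to rule it out, not a description of the trial's planned test.
- **Detail may sit in a fuller document.** Coding and covariate lists often do. But this text itself puts several tests of the same outcomes under one threshold; that is a statement, not a silence.

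**Conclusion.** The point holds as an analysis choice that should be settled. The plan presents overlapping tests of the same outcomes without naming the one that decides the primary outcome, and it states no adjustment for a baseline score that every randomized participant has.

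For the same contrast, baseline adjustment takes power from about 0.80 to 0.84–0.98 at a single visit, or from 0.94–0.86 to about 0.97–0.997 for the follow-up average, as r runs from 0.3 to 0.7. The direction holds for any r above zero; the size rests on the assumed r, equal correlations and an equal effect at both visits. The Background section expects single-session effects to wane, and if they do, the follow-up average loses some of its advantage over the earlier visit.

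The 11 to 19% false-positive range should not be read as the trial's error rate. It depends on which tests are counted and on a rule, that any significant result may be claimed, which the document does not state. It measures what the open choice would allow. The platform term serves mainly to match the analysis to the allocation.

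**What to change.** In the Data analyses section, name one primary model: a repeated-measures model (GEE or mixed) of ACQ-EC at 2 and 8 weeks, with arm, time, arm-by-time, baseline ACQ-EC and platform as fixed effects, and correlation within participant. University may replace platform, and neither need be added if university is already a level of the model.

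Name one deciding arm contrast in advance: 2 weeks, 8 weeks or their average. The choice is the sponsor's. The average is the more powerful if the effect persists; a single visit answers a more specific question.

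Use the same model for the secondary outcomes. Say whether the t-tests and ANOVA are baseline description. Label any other analysis as sensitivity or descriptive, and state that neither the group main effect nor the time effect is a test of the treatment effect.

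The cost is a change of wording, to be dated before the arms are compared. It needs no new data and no further recruitment.
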